## Primary and secondary outcomes

The primary outcome of the study will be adherence to school feeding, obtained from the answers given by the students in question about the frequency of school meals consumption through 1 week, applied by the researchers in three moments (baseline, half of the school year and by the end of the school year). The secondary outcome will be the acceptance of school feeding through the acceptability tests referring to the dishes inserted in the menus established in 2019 in the schools participating in the study, applied after the fourth week from the beginning of each menu. (Fig.1).

All data collected in this study will be entered in duplicate and managed using Epi-Info software, version 3.5.1 (CDC, Atlanta, GA, USA). Access to information will be limited to designated members, such as researchers. Paper documents such as consent forms, questionnaire answer sheets and anthropometric measurements will be stored on a hard disk.

## Statistical analysis

Statistical analyses for each outcome will be performed using generalized linear models that takes into account repeated measurements and missing data. The models will be used to assess the impact of the intervention and will include 3 main variables: intervention (intervention 1, intervention 2 or control school), time (treated as continuous, in months) and the intervention x time interaction. Data analysis will be performed using the SAS OnDemand for Academics (SAS Institute Inc., Cary, NC, USA).

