## Methods

### Study design

This is a multi-component school-based, clinical trial called PAPASS, which means “Professionals and Students for Healthy Eating in Sumidouro”. PAPASS is a study aimed at increasing adherence and acceptance of school meals, which will be conducted in the 2019 school year in 3 public schools in the city of Sumidouro, Rio de Janeiro, Brazil. All students from 4th to 9th grade, morning and/or afternoon shifts from the 3 selected schools will be invited to participate in the study.

The study design will be parallel, with 3 arms: (1) Control group (without intervention); (2) Intervention group 1 (changes in the school environment) and (3) Intervention group 2 (changes in the menu and school environment) (Fig.1). To allocate interventions, schools will be numbered and randomly allocated to each group using opaque envelopes by people who are not involved in PAPASS.

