### Sample size calculation

The sample size of the PAPASS study was calculated based on the results of the last edition of National School Health Survey, conducted in 2015, which revealed that only 37.21% of Brazilian students, from 6th to 9th grade, from public schools, morning or afternoon shifts, that reported the availability of school meals, consume them at least three times a week [10, 28]. Considering a 50% increase in adherence to school meals, 80% power and a significance level of 5%, a sample size of 109.4 adolescents per arm was estimated, totaling a sample of 328.2 students. Considering losses and the rate of refusal, the total sample size required was increased by 20%, raising to approximately 132 students in each arm and a total of 396 students in the sample.

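### The stated model names no clustering above the pupil, so standard errors for the arm-by-time term will be too small if change in adherence differs between classes

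*Protocol article*

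**What the plan says.** All places are in the protocol article.

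- **Statistical analysis:** "Statistical analyses for each outcome will be performed using generalized linear models that takes into account repeated measurements and missing data". The section then lists three model terms: arm, time in months as a continuous variable, and arm by time. It names no class, grade, shift or school effect and no cluster-robust variance.
- **Study design:** allocation is by school, one school to each of three arms ("schools will be numbered and randomly allocated to each group using opaque envelopes"). Those invited are "All students from 4th to 9th grade, morning and/or afternoon shifts from the 3 selected schools".
- **Data collection at school:** adherence (school meals on three or more days a week) is asked in March, August and November. The list of data to be collected does not name class, section or shift.
- **Sample size calculation:** "a sample size of 109.4 adolescents per arm was estimated, totaling a sample of 328.2 students", and then "the total sample size required was increased by 20%, raising to approximately 132 students in each arm". No ICC or design effect appears.

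**The concern.** Each school contributes intact groups: six grades if all are present, possibly split by shift. Pupils in one class share a timetable, peers and the same cafeteria sitting, so weekly use of school meals could plausibly move up or down for a class together. This dependence sits between the pupil and the school. It is a separate matter from having one school per arm, and unlike between-school variance it can be estimated from the trial's own data.

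The arm-by-time term compares changes. What matters is therefore not whether classes differ in their level of adherence, but whether they differ in how adherence changes from March to November. If they do, a model that treats each pupil's change as independent overstates the information. A few classes changing their habits for reasons unrelated to the intervention could then be reported as an effect on the primary outcome.

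**Working it through.** **1. The plan's own sample size.** Inputs from the Sample size calculation section: baseline adherence 37.21%, a 50% relative increase, 80% power and a 5% significance level (two-sided assumed, as the article does not say).

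- p1 = 0.3721; p2 = 1.5 × 0.3721 = 0.5582; difference 0.1861.
- Unpooled variance: n = (1.960 + 0.842)² × (0.3721 × 0.6279 + 0.5582 × 0.4418) / 0.1861² = 108.9 per arm.
- Pooled variance under the null: 111.6 per arm.
- Stated: 109.4. The two results bracket it, 0.5% below and 2% above. One-sided (88) and continuity-corrected (123) calculations do not fit.
- 109.4 × 1.2 = 131.3, stated as 132; 132 × 3 = 396.

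The stated size thus corresponds to independent pupils, with a design effect of 1. A design effect of only 1.10 would already give 108.9 × 1.10 = 119.8. The sample size is therefore consistent with an analysis that has no level above the pupil.

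**2. Size by formula.** The article gives no class size and no ICC, so both are assumptions: 132 pupils per school in 12 classes of 11 (grade by shift) or 6 classes of 22 (one per grade), and an ICC of change of 0.01 to 0.05.

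Design effect DE = 1 + (m − 1) × ICC. True two-sided error of a nominal 5% test = 2 × [1 − Φ(1.96/√DE)].

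| Class size m | ICC of change | DE | True error | 132 pupils are worth |
|---|---|---|---|---|
| 11 | 0.01 | 1.10 | 6.2% | 120 |
| 11 | 0.02 | 1.20 | 7.4% | 110 |
| 11 | 0.05 | 1.50 | 11% | 88 |
| 22 | 0.01 | 1.21 | 7.5% | 109 |
| 22 | 0.02 | 1.42 | 10% | 93 |
| 22 | 0.05 | 2.05 | 17% | 64 |

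At ICC = 0 the design effect is 1 and the test is correct.

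**3. Simulation of a model with the planned terms.** Logistic GEE with arm, continuous time (0, 5 and 8 months) and arm by time, clustered on the pupil. Three schools of 6 classes of 22, pupil random-effect SD 1.2 on the logit, no arm effect, 300 runs per setting.

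| Class level SD | Class change SD over 8 months | Mean model SE | True SD of estimate | Rejections at 5% |
|---|---|---|---|---|
| 0 | 0 | 0.0389 | 0.0393 | 6.3% |
| 0.6 | 0 | 0.0384 | 0.0385 | 5.7% |
| 0.6 | 0.3 | 0.0385 | 0.0440 | 8.3% |
| 0.6 | 0.6 | 0.0388 | 0.0476 | 12.3% |

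The second row shows that a stable class effect does no harm. In the last two rows the model SE is too small by a factor of 0.0440/0.0385 = 1.14 and 0.0476/0.0388 = 1.23. With 300 runs, the Monte Carlo standard error of a 5% rejection rate is √(0.05 × 0.95/300) = 1.3 percentage points, so these rates are approximate.

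**4. Simulation of a simpler analysis.** Two schools, no true effect, 4,000 runs, testing pupil change scores with a pupil-level standard error. This is not the planned model, but it checks the formula. With 6 classes of 22, the error was 5.3% with no class effect, then 8.4%, 10.5% and 18.4% at ICCs of change of 0.014, 0.025 and 0.054. With 12 classes of 11 at similar ICCs it was 7.4%, 8.5% and 11.3%. A t test on class-mean changes held 4.4% to 5.4% throughout.

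**The case against.** **The article is condensed.** A fuller plan may hold a class effect or a class-robust variance, and the text does not say that repeated measurement is the only dependence allowed for. A reader might infer that class clustering has been ruled out; the article does not support that. What remains is that the section does state the model terms and the dependence handled, and the sample size agrees with that reading. An analyst who follows the text as written will ignore class.

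**The intervals need not be too narrow.** A reader might infer that they certainly are. The article gives no figure for class differences in change, and with stable class effects the simulated model SE was right. This objection stands, and the point is conditional for that reason.

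**The classes may be regarded as fixed.** All eligible pupils of the three schools are invited. If inference stops at those schools and their existing classes, class variation is not necessarily sampling error. That would carry weight if the trial's claim stopped there. The Discussion section, however, says that a positive result would support implementation across the municipality's school system and the country, which does not treat the enrolled classes as fixed.

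**The larger flaw is elsewhere.** With one school per arm, arm and school cannot be separated, and class-adjusted intervals do not change that. This also stands. A reader might take adjusted intervals as a valid basis for attributing a difference between schools to the intervention, and they would not be.

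**Conclusion.** The point holds in conditional form. The stated model includes no clustering above the pupil, although intact grades and shifts are enrolled, and its standard errors for the arm-by-time term will be too small if change in adherence differs between classes.

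The formula range of about 6% to 17% true error rests on assumed class sizes, an assumed ICC of change and 132 pupils per school, which is the required number and not known enrolment. For a model with the planned terms, the range shown is 8% to 12%. The two ranges scale the class effect differently and are not directly comparable; in particular, the 17% figure comes from the formula and has not been shown for the planned model.

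The matter should be corrected because the remedy is simple, but it ranks below the confounding of arm with school.

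**What to change.** 1. Record each pupil's class (grade, section and shift) in the data set. The choice of hedonic card separates only two grade bands and applies to pupils who eat in the cafeteria, so it cannot supply this for the adherence questionnaire.
2. Amend the Statistical analysis section in one of two ways: (a) GEE with class as the cluster for the variance, a small-sample correction and a t reference; or (b) a mixed model with pupil random effects and class-by-wave (or class-slope) random effects.
3. As a check, compare class-mean changes between arms by t test.
4. State in the same place that this handles within-school dependence only, and that arm remains fully confounded with school because there is one school per arm.

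**Cost:** a few sentences in the analysis section and one added variable. Intervals will be wider and degrees of freedom fewer: for a two-arm contrast about 2 × 6 − 2 = 10 with six classes per school, or 2 × 12 − 2 = 22 with twelve.

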However, providing food allowance for students enrolled in the public school system does not guarantee that adherence to the program is satisfactory in Brazil. Results from the 2012 National School Health Survey (PeNSE) indicated that only 22.8% of 9th graders in public schools consumed school meals at least 3 days a week [9]. In a new edition from PeNSE, conducted in 2015, revealed that only 31.3% of Brazilian students enrolled in the 9th grade of public schools consumed school meals on at least 3 days of the week [10], being classified as low adherence to school feeding [11].

Acceptance of school meals (approval of the dish offered) is another important factor, once it reflects the quality of services provided by schools and refers to the average preference of foods offered by them [12]. According to the National Education Development Fund (FNDE), menus must be prepared by nutritionists, based on students’ eating habits, and should have 85 to 90% acceptance [12, 13]. Silva et al. (2013), in a study conducted with 1448 students from the state school system of Minas Gerais, Silva et al. (2013) observed that the effective acceptance, answers considered as “excellent” and “very good”, reached only 28.8% [14].

In an integrative literature review, which aimed to identify the factors that influence the adherence and acceptance to school meals among Brazilian students, it was observed that, the most relevant ones were socioeconomic variables, nutritional status, age, presence of competitive foods in the school environment, behavioural factors such as changes in dietary practices and choices, as well as inadequate preparation for eating habits [15]. In this context, the school has the role of educating, as well as making individuals aware of the countless possibilities of healthy consumption, more attentive to their practices and eating habits [13, 16–18].

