### Data collection at school

Data on the characteristics of the study population (age, gender and skin color/ race), anthropometric measures, socioeconomic data, physical activity practice, sedentary habit, breakfast habit, food intake and adherence to school feeding will be collected in three moments (baseline - March, half of the school year – August, and end of the school year - November), using a structured questionnaire applied by trained researchers. Acceptability tests will be performed bimonthly, in order to include all menus established in the schools participating in the study.

Adherence will be assessed through a specific question in the questionnaire directed to the frequency of school meals consumptionin the week, with the options: never, once a week, twice a week, three times a week, four times a week or all days. Students who consume the food offered 3 or more times a week will be considered as adhering to the school feeding program [9]. Each adolescent will be assessed in 3 moments: at baseline - at the beginning of the school year; the second - at half of the school year; and the third - at the end of the school year. In order to avoid follow-up losses, schools will be visited 4 times at each moment of data collection (Table 1).

**Table 1 Tab1:** Intervention components, description and assessment

Intervention components	Description	Assessment
Adherence to school meals	- Placement of posters on cafeteria walls and displays on tables with messages and/or images that encourage students to make healthier food choices; - The implementation of the use of tablecloths in the cafeteria with color images of fresh foods, accommodation of the fruits served in the school feeding in a prominent position, improving their visibility in an attractive way; - The equipment of the cafeterias, with the installation of a thermal distribution counter to guarantee the autonomy of food choice by the students, through a self-service system; - Placement of a banner with the daily dishes menu at the entrance of the cafeteria; application of footprints on the floor that playfully direct the adolescents to the cafeteria; - Changes in the dishes that make up the menu of the only school which will receive the two interventions (Intervention group 2).	A question about the frequency of school meal consumption, applied in 3 moments (baseline, half of the school year and end of the school year).

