### Intervention

The interventions will take place during the 2019 school year, beginning in April, in the two schools allocated to the intervention groups and will combine two strategies: modifications in the school environment and modifications in the menu offered by the school. Interventions in the environment will be based on the choices architecture principles proposed by Thaler & Sustein [23, 37, 38], and the interventions in the menu will be based on the factors that contribute to poor adherence and acceptance of school feeding, identified through a previously conducted focus groups with the lunch ladies (school food service employees) of the all 3 participating schools and the students of the school that will receive the two interventions (intervention group 2).

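### The stated effect model names no adjustment for grade or socioeconomic level, so with one school per arm, year-long trends that differ by pupil mix can enter the intervention x time term

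*Protocol article*

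**What the plan says.** The Protocol article's Statistical analysis section describes generalized linear models for each outcome that allow for repeated measurements and missing data. They "will include 3 main variables: intervention (intervention 1, intervention 2 or control school"), then "time (treated as continuous, in months) and the intervention x time interaction". The Methods part of the Abstract repeats these three terms. No covariate is named in either place.

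Four other parts of the article bear on this:

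- **Allocation** (Study design): "schools will be numbered and randomly allocated to each group using opaque envelopes". There are three schools and three arms, hence one school per arm. On recruitment: "All students from 4th to 9th grade, morning and/or afternoon shifts from the 3 selected schools will be invited".
- **Determinants** (Background): a literature review of influences on adherence and acceptance is summarised as "the most relevant ones were socioeconomic variables, nutritional status, age, presence of competitive foods in the school environment", among others.
- **Data held** (Data collection at school): "Data on the characteristics of the study population (age, gender and skin color/ race), anthropometric measures, socioeconomic data" and further items "will be collected in three moments (baseline - March, half of the school year – August, and end of the school year - November". Grade is known from enrolment.
- **Timing** (Intervention): "The interventions will take place during the 2019 school year, beginning in April". The March wave therefore precedes the intervention.

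**The concern.** Drawing one school for each arm is a fair draw, but it gives no expectation of similar pupils within this one allocation. The three schools may differ in the share of younger and older grades or in socioeconomic level. The protocol says such factors matter for the outcome and collects them, yet the model it states uses none of them.

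The term that carries the effect is intervention x time. If older pupils, say, drift away from school meals during the year, a school with more of them will show a steeper fall whatever its arm. The three-term model has no term that could attribute that fall to grade, so it goes into the interaction. The bias can take either sign, depending on which school has which mix. The article intends a positive result to support use across the municipality and the country, so the reading of that one term matters.

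**Working it through.** **1. The planned effect, as a yardstick.** From Sample size calculation: control adherence 37.21%, a 50% relative increase, 80% power, 5% significance (taken as two-sided).

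- p1 = 0.3721; p2 = 1.5 x 0.3721 = 0.55815; difference 18.6 points.
- Odds ratio = (0.55815/0.44185) / (0.3721/0.6279) = 2.13.
- Unpooled formula: n = (1.960 + 0.842)^2 x [0.3721 x 0.6279 + 0.55815 x 0.44185] / 0.18605^2 = 108.9 per arm. The pooled-null version gives 111.6. The stated 109.4 lies between them, and 109.4 x 1.2 = 131.3 agrees with 132 per arm and 396 in total. The sample size figure is not in question here.

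**2. Set-up for the check.** The article gives no school composition, so these inputs are assumed:

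- The true intervention effect is zero.
- A binary pupil characteristic X has prevalence 50% v 60%, 40% v 60% or 30% v 70% in two schools.
- X lowers the odds of adherence by a factor of 1.5 to 3.
- Pupils without X start at 37.21%.
- A common time trend has odds ratio 1 or 1.5 from March to November.
- The X x time odds ratio is 1 (no differential trend), 1.5 or 2 over the same period.

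For a school with prevalence q, adherence at time t is (1 - q) x P(t | X=0) + q x P(t | X=1). The spurious interaction is the November odds ratio between schools divided by the March odds ratio.

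**3. X affects level only (X x time odds ratio 1).**

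- March odds ratio between schools: 0.65 to 0.96. This goes into the arm main effect.
- Spurious interaction odds ratio: 0.997 to 1.000, at most 1.4 points on the risk scale.

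**4. X also changes the trend (X x time odds ratio 1.5 to 2).** One case in full, with prevalence 40% v 60%, X halving the odds, no common trend and X x time odds ratio 2:

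- X=0: 0.3721 in March and November (odds 0.5926).
- X=1: March odds 0.5926/2 = 0.2963, so 0.2286; November odds 0.2963 x 2 = 0.5926, so 0.3721.
- School with 40%: March 0.6 x 0.3721 + 0.4 x 0.2286 = 0.3147; November 0.3721.
- School with 60%: March 0.4 x 0.3721 + 0.6 x 0.2286 = 0.2860; November 0.3721.
- Difference in change: 0.3147 - 0.2860 = 2.87 points; interaction odds ratio 1/0.872 = 1.146.

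Over the whole grid the spurious interaction odds ratio is 1.04 to 1.32, or 0.4 to 6.4 points. Against the planned effect that is 0.4/18.6 = 2% to 6.4/18.6 = 34%.

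**5. A plainer version, also assumed.** Suppose adherence falls 10 points over the year in grades 6-9 and not in grades 4-5, and grades 4-5 make up 50% of one school and 20% of another. The schools then differ in change by (0.50 - 0.20) x 10 = 3 points, or 3/18.6 = 16% of the planned effect.

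Losses that depend on grade or socioeconomic level are a second route to the same term. They were not quantified.

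**The case against.** The strongest reply is that this is an article with a very short analysis section, and that adjustment sets are commonly left to a full protocol or SAP. That stands in part. A reader might infer that the model is restricted to three terms and that covariates are ruled out, but the text lists main variables and does not say that nothing else may enter. What remains is that the effect model is stated twice and neither statement provides for these factors.

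A reader might also infer that any difference in pupil mix between schools biases the effect. The documents do not support that: with a March wave before the April start and an arm main effect, level differences stay out of the interaction (step 3). Nor do they show that the schools are non-equivalent. No composition by school is reported, and imbalance is a risk of having one school per arm, not a recorded fact. The Background says age and socioeconomic variables influence adherence and acceptance. It does not say they alter the trend within a year.

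A gain in precision might be claimed for adjustment as well. That should not be relied on: under a logit link, adding prognostic covariates does not generally shrink the standard error of the log odds ratio, and it changes the quantity estimated.

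Finally, pupil-level adjustment cannot separate intervention from school when each arm is one school. That is true and is the more basic limitation. It restricts what the adjustment can achieve, but it is no reason to leave out the measured part.

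**Conclusion.** The point holds in a limited form. The stated model has no provision for trends or losses that differ by grade, age or socioeconomic level, although the protocol treats age and socioeconomic variables as relevant and has the data. Stable differences in mix are not the problem. Differential trends are, and only if the schools also differ in mix. Under the assumed prevalences and odds ratios the spurious change is 0.4 to 6.4 points (odds ratio 1.04 to 1.32), against a planned 18.6 points (odds ratio 2.13). The bias could therefore be trivial or up to about a third of the planned effect, and the article does not allow a closer figure. It is worth correcting because the remedy is cheap and because covariates chosen after the data are seen would carry less weight. No stated number is wrong.

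**What to change.** In Statistical analysis, prespecify an adjusted model for the primary outcome. To intervention, time and intervention x time, add baseline grade (or baseline age), the March socioeconomic score, grade (or age) x time and socioeconomic score x time. The time interactions are the essential part, since covariate main effects alone would barely move the intervention x time term. Report the three-term model alongside it, and say in advance which of the two carries the conclusion.

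Add a sentence stating that this removes only the measured part of differential trends and that, with one school per arm, no pupil-level adjustment can separate the intervention from the school.

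The cost is small. No new data are needed, and there are four extra parameters if grade and score enter as linear terms (two main effects and two time interactions), or more if grade is categorical. If the link is logit, the adjusted odds ratio is conditional rather than marginal, so it is not directly comparable with the three-term odds ratio, and the report should say so.
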